### 3.2. Participants

#### Sample and Recruitment

The sample will consist of adults (≥18 years) with a confirmed diagnosis of malignant neoplasm admitted to the Oncology Ward of the Hospital Clínico Universitario de Salamanca, recruited consecutively during the period March–November 2026. Eligible patients must have an expected hospital stay of at least 5 days, a functional status of 0–2 according to the Eastern Cooperative Oncology Group (ECOG) scale, and the ability to provide informed consent, complete questionnaires, and perform voluntary contractions required for functional testing. These criteria were established to ensure participant safety, feasibility of assessments, and data quality in the context of repeated bedside neuromuscular evaluations.

Exclusion criteria include contraindications to strength assessment, such as recent fractures, acute musculoskeletal injuries, or pain limiting safe performance of the tests. Patients with severe neurological impairment preventing reliable functional assessment or significant cognitive deficits affecting comprehension or adherence to instructions will also be excluded. In addition, participants with implanted electronic devices will not be included, in accordance with the contraindications or precautions for bioimpedance measurements. Patients with extensive skin lesions or dermatological alterations at electrode placement sites that prevent safe and proper surface electromyography (sEMG) recordings will be excluded.

Cancer stage and current treatment (chemotherapy, immunotherapy, radiotherapy, or supportive care) will be recorded.

A consecutive sampling strategy will be used. Potential participants will be identified in coordination with the medical team, with oncologists referring eligible patients according to the inclusion and exclusion criteria. Nursing staff will also collaborate by providing relevant clinical and care information and by facilitating the scheduling of assessments at times compatible with routine patient care.

A screening log will be maintained throughout the recruitment period to document the number of patients assessed for eligibility, reasons for exclusion, refusal to participate, and recruitment outcomes. When available, basic demographic and clinical information of excluded patients will be summarized in aggregate form to assess the representativeness of the recruited cohort.

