To provide a broader characterization of factors potentially influencing muscle deterioration, the following variables will be recorded whenever available from the medical record: cancer stage, reason for hospital admission, recent anticancer treatment and treatment timing, corticosteroid exposure, opioid or sedative medication use, nutritional support interventions, clinically significant infection or inflammatory complications, anemia status, mobility restrictions, and hydration-related factors, including edema, ascites, and intravenous fluid administration.

Surface Electromyography (sEMG)

Electromyographic activity was recorded using the wireless Shimmer3 system, integrated into the mDurance platform [36]. Signals were acquired at a sampling frequency of 1000 Hz, ensuring adequate temporal resolution for amplitude and frequency parameter analysis.

A band-pass filter between 10 and 500 Hz was applied to remove low-frequency components and high-frequency noise, along with a 50 Hz notch filter to suppress electrical interference. Acquisition and preprocessing parameters were kept constant across all assessments to ensure intra- and inter-subject comparability.

Skin preparation and electrode placement were performed according to SENIAM guidelines. Electrodes were positioned on the vastus lateralis, vastus medialis, and upper trapezius. The vastus lateralis and medialis were selected due to their key role in functional mobility and load transfer during activities of daily living, as well as their documented sensitivity to accelerated muscle loss in prolonged disuse and bed rest contexts [37,38,39]. The upper trapezius was chosen as an accessible postural muscle relevant during prolonged sitting, allowing evaluation of fatigue patterns distinct from those of the lower limbs [40,41].

Lower limb protocol: Three maximal voluntary contraction (MVC) attempts of 3 s each will be performed, with 2 min rest intervals between attempts. Subsequently, an isometric contraction at 65% of MVC will be maintained using biofeedback via a portable dynamometer until muscle failure, defined as the inability to maintain the target intensity (±5–10%) for more than 3–5 consecutive seconds despite visual/auditory feedback [42,43].

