Neuromuscular fatigue indices were calculated as follows: Temporal slope of MDF during sustained contraction; Final/initial RMS ratio, as an indicator of changes in muscle activation; Time to failure, defined as the moment when the participant was no longer able to maintain the target force level; failure was considered when force decreased persistently by more than 5–10% below 65% of MVC during the isometric contraction [43,44].

During data acquisition, real-time visual inspection was performed to detect artifacts (movement, electrical interference, or loss of electrode contact), complemented by a systematic post-acquisition review to ensure the quality and consistency of the recordings prior to final analysis.

sEMG Acquisition and Signal Processing Procedures

All assessments will be performed with participants seated comfortably in a chair or hospital bed with back support. For quadriceps recordings, hips and knees will be positioned at approximately 90° flexion whenever clinically feasible, while for upper trapezius recordings, participants will remain seated with arms relaxed alongside the body. Standardized positioning will be maintained across sessions whenever possible.

Surface electromyography (sEMG) electrode placement will follow SENIAM recommendations. Bipolar Ag/AgCl surface electrodes will be positioned parallel to muscle fiber orientation with an inter-electrode distance of 20 mm. Skin preparation will include shaving, when necessary, gentle abrasion, and cleaning with alcohol to reduce impedance.

Force measurements and sEMG signals will be recorded simultaneously and synchronized through the acquisition software. Raw signals will be visually inspected prior to analysis to identify artifacts and signal abnormalities.

Signal processing will include band-pass filtering, full-wave rectification, and frequency-domain analysis using Fast Fourier Transform (FFT) techniques. Spectral analyses will be performed using Hamming windows of 1024 samples with 50% overlap. Mean and median frequency parameters will be calculated from consecutive one-second epochs during the sustained contraction task.

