Prior to analysis, all recordings will undergo visual inspection and quality-control procedures. Signal segments will be excluded if they exhibit evidence of electrode displacement, signal saturation, excessive baseline noise, movement artifacts, abrupt signal discontinuities, or other technical abnormalities that may compromise signal interpretation. When multiple epochs are available, only artifact-free segments meeting predefined quality criteria will be included in the final analysis.

To ensure reliability in the bedside hospital setting, all evaluators will undergo standardized training, and all procedures will follow predefined operating protocols. Electrode placement sites will be systematically documented to ensure consistent positioning across repeated measurements.

Safety Monitoring and Adverse Event Recording

All assessments will be performed only when participants are considered clinically stable by the attending medical team. Prior to each testing session, patients will be screened for contraindications, including acute clinical deterioration, uncontrolled pain, severe fatigue, hemodynamic instability, active infection requiring urgent intervention, or any condition that may compromise safe participation.

Adverse events occurring during or immediately after testing will be documented, including dizziness, excessive fatigue, pain exacerbation, musculoskeletal discomfort, cardiovascular symptoms, falls, or any unexpected clinical event. The severity, duration, and relationship to the assessment procedure will be recorded.

Testing will be immediately discontinued if participants report intolerable discomfort, request termination, exhibit signs of excessive fatigue, develop cardiovascular symptoms, or if the research team determines that continuation may compromise safety. Participant safety will always take precedence over protocol completion.

Serum biomarkers—Basic Panel

Laboratory assessments will be performed at hospital admission and discharge. In cases where daily blood tests are required for clinical reasons, these additional results will be incorporated into the longitudinal analysis.

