### 3.5. Procedure

Following the identification of eligible patients by the Oncology team and verification of inclusion and exclusion criteria, participants will receive detailed information about the study and will provide written informed consent prior to any study-specific procedures.

Assessments will be conducted in the patient’s room, either self-administered or assisted by a researcher following a standardized script to ensure consistency in data collection (Table 1).

On the day of admission (Day 1), a comprehensive baseline assessment will be performed, including questionnaires (SARC-F, EORTC QLQ-C30, and PSQI), HGS measurement, body composition assessment using bioelectrical impedance, electromyographic recording of selected muscles, and blood sampling for serum biomarker determination.

From Day 2 until the penultimate day of hospitalization, daily functional assessments will be performed, consisting of HGS measurement and an sEMG protocol for neuromuscular fatigue characterization. These assessments will be scheduled in coordination with the clinical team to avoid interference with medical or therapeutic procedures.

On the day of hospital discharge, the full assessment performed at admission will be repeated, allowing analysis of absolute admission-to-discharge changes in both primary and secondary outcomes.

All evaluations will follow previously described standardized procedures, including quality control measures, periodic equipment calibration, and systematic recording of clinical events that may influence measurements. The assessment schedule (Table 1) is designed to integrate into routine clinical practice, minimizing patient burden while always ensuring safety.

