## 4. Study Relevance

The protocol will provide characterization of trajectories of muscle deterioration; exploratory evaluation of biomarker profiles associated with muscle deterioration; neuromuscular fatigue parameters to differentiate muscle loss from dysfunction; relationships between sleep, symptom burden, and function; and evidence regarding the feasibility of multimodal assessment in real-world hospitalization settings. The findings of this study may help identify candidate variables associated with hospitalization-related muscle deterioration and provide preliminary data to support the design of future prospective and hypothesis-driven studies investigating potential determinants and mechanisms of muscle deterioration in hospitalized oncology patients.

Repeated fatigue assessments may impose an additional burden on some hospitalized oncology patients. Potential sources of measurement variability include learning effects, day-to-day fluctuations in clinical status, and incomplete protocol adherence due to fatigue or medical complications. For this reason, feasibility outcomes, protocol adherence, adverse events, and reasons for missed or interrupted assessments will be systematically recorded to inform future optimization of the assessment strategy.

The findings of this study may help identify candidate variables associated with hospitalization-related muscle deterioration and provide preliminary data to support the design of future prospective studies aimed at developing and validating predictive models.

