## Figures and Tables

**Table 1 biomedicines-14-01504-t001:** Assessment schedule.

Assessment	Screening	Admission	Daily	Discharge
Eligibility criteria	X			
Informed consent		X		
Demographic and clinical data		X		
Cancer characteristics		X		
Weight		X	X	X
BMI		X		X
Dietary intake			X	
Handgrip strength		X	X	X
sEMG assessment		X	X	X
Bioelectrical impedance analysis		X	X	X
Fatigue questionnaires		X	X	X
Quality of life measures		X		X
Sleep assessment (PSQI)		X		X
Biomarkers/laboratory parameters		X	X	X
Adverse events			X	X
Hydration-related variables		X	X	X

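### The adverse event window stops immediately after each test session and does not match Table 1, so delayed or cumulative effects of daily testing may go unrecorded or unattributed

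*Protocol article*

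**What the plan says.** The subsection on safety monitoring in section 3.4 (Instruments) sets the recording rule: "Adverse events occurring during or immediately after testing will be documented". The following sentence adds that "The severity, duration, and relationship to the assessment procedure will be recorded". The list of example events is open and ends with a general category for unexpected events. Electrode-site skin reactions are not named in it.

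The exposure is repeated. For the lower limb, after three maximal attempts, "an isometric contraction at 65% of MVC will be maintained using biofeedback via a portable dynamometer until muscle failure"; the upper trapezius follows the same pattern. Section 3.5 places the first sEMG recording on the day of admission and repeats the whole assessment at discharge. In between, "From Day 2 until the penultimate day of hospitalization, daily functional assessments will be performed", and these include the sEMG fatigue protocol. On the skin, "Skin preparation will include shaving, when necessary, gentle abrasion, and cleaning with alcohol to reduce impedance", at sites that are documented so that they stay the same.

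Table 1 has a row "Adverse events" marked under Daily and Discharge, with nothing under Admission. Section 4 accepts that "Repeated fatigue assessments may impose an additional burden on some hospitalized oncology patients" and says adverse events, adherence and reasons for missed sessions will be recorded to improve the assessment strategy.

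**The concern.** The written window closes at the point where effects of repetition would begin to show. Muscle soreness the next day, a fall later on the day of testing, and skin irritation after several preparations of one site would all tend to appear between sessions. Section 3.2 treats skin condition as relevant at entry, excluding "Patients with extensive skin lesions or dermatological alterations at electrode placement sites" where recording would not be safe and proper. The event list, however, does not name a skin reaction that the preparation itself might cause.

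The stake is the tolerability evidence. The study intends to learn from adverse events whether daily testing is workable and how to adjust it, and this rule is weakest for the harm most specific to daily repetition. A smaller, secondary stake is interpretation of the exploratory sEMG trajectories. Section 3.11 presents the tested muscles as informative about general neuromuscular deterioration, and carry-over from the previous day's test is not among the sources of variability named in section 4.

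**Working it through.** The plan states no figure on this point, so there is none to reproduce. The check sets the passages side by side and then counts exposure.

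**Passages compared**

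- *Safety subsection, section 3.4.* Defines which events are documented: those in or directly after a session. Severity, duration and relationship to testing attach to these.
- *Table 1.* Shows when adverse events are recorded: Daily and Discharge. It marks sEMG separately under Admission, Daily and Discharge, and section 3.5 starts the daily assessments on Day 2. The Daily column therefore does not cover the admission session, and that session has no adverse event mark. Under the text it should have one.
- *Pre-session screen, section 3.4.* Looks for uncontrolled pain, severe fatigue and other conditions that make testing unsafe. Its stated purpose is to decide whether to test. Nothing says that a positive finding becomes an adverse event or is related to the previous session.
- *Section 3.5.* Calls for recording clinical events that could affect measurements, with no time limit but also no assessment of relationship to testing.
- *sEMG protocol, section 3.4.* Documents the reason for any change of contraction intensity at each assessment.
- *Section 4.* Records adverse events and reasons for missed or interrupted sessions, without widening the definition.

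So a delayed effect can be noticed at the next visit and may be written down somewhere. No passage ensures that it is recorded as an adverse event with its relationship to testing.

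**Exposure**

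Inputs: an expected stay of at least 5 days (section 3.2), three muscles and two sustained tasks per session (section 3.4), and a target of 50 participants (section 3.2). Assumptions: one session a day, none omitted, one side prepared, and an actual stay of exactly 5 days.

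- Sessions per patient: 5; contractions to failure: 5 × 2 = 10; between-session intervals: 5 − 1 = 4.
- Site preparations per patient: 5 × 3 = 15.
- In 50 patients: 250 sessions, 500 contractions to failure, 750 site preparations and 200 between-session intervals.
- For a 10-day stay, per patient: 20 contractions to failure and 9 intervals.

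These are illustrative counts and not minimums. The 5 days is an expected stay, and section 3.6 allows sessions to be omitted.

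**Secondary sEMG point**

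Section 3.4 normalises RMS to the maximal contraction and sets the sustained target as a percentage of it. If soreness from one session lowered the maximal contraction at the next, it would enter both quantities. If it led to suspension for pain under section 3.6, the gap would be handled under the missing-at-random assumption in section 3.9 with no required note that testing was the cause. Whether this happens, and how often, cannot be derived from the documents.

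**The case against.** The best reply is that the plan already has several ways of catching delayed effects: adverse event marks at each daily visit and at discharge, a screen before every session, recording of clinical events that could affect measurements, documented reasons for reduced intensity, and reasons for missed sessions. The event list and the screen both end in a general category, so a skin reaction is not excluded. Shaving is done only when needed and abrasion is described as gentle. A condensed article may also leave look-back questions and form items to operating procedures that are not shown.

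Much of this stands. A reader might infer that events are captured only within sessions and that later harm goes unrecorded altogether. The passages above do not support that; the defensible claim is that such harm may be missed or not attributed. A reader might also infer that test-induced fatigue biases the main result. The documents give no route to it: the primary outcome is dominant-hand grip, and the muscles held to failure are the quadriceps and upper trapezius. Nor can one say what share of the day is observed. Reading the window as one hour gives 1/24 = 4.2% and as 15 minutes 0.25/24 = 1.0%, but both lengths are guesses and both ignore the other recording duties.

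The reply does not remove the point. The article does state a window, that window conflicts with its own schedule, and no other passage links findings between sessions to testing. This is a stated rule that needs correcting, not a detail left to another document.

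**Conclusion.** The point holds as a modest, cheap improvement. The window in the safety subsection and the adverse event row of Table 1 disagree and must be reconciled, including at Admission. As written, delayed or cumulative effects of daily testing may go unrecorded or be recorded without relationship to testing, which weakens the tolerability data that section 4 intends to use. Under the stated assumptions, 200 between-session intervals in 50 patients lie outside the written window. That number describes opportunity for missed events, not the number missed. The size of any bias in the sEMG trajectories cannot be computed, those outcomes are exploratory, and no effect on the primary handgrip endpoint is claimed.

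**What to change.** 1. Reconcile the safety subsection of section 3.4 with Table 1, and add the adverse event mark at Admission.
2. Define the recording window as running from the start of a session until the next session or, after the last one, until the patient leaves the ward. State that events after discharge are not observed.
3. At the existing pre-session screen, record events since the previous session (soreness in tested muscles, falls, electrode-site skin reactions) with their relationship to testing, and name electrode-site reactions in the event list. This concerns recording only; no rule for withholding or changing testing is proposed.
4. For the exploratory sEMG outcomes, name carry-over from repeated testing as a possible explanation for change, and repeat the trajectory analysis without sessions preceded by recorded test-related soreness.

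The cost is a few form items, an estimated one to two minutes at visits already planned, one additional exploratory analysis, and a slightly higher count of minor events. No visit or procedure is added.

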### 3.5. Procedure

Following the identification of eligible patients by the Oncology team and verification of inclusion and exclusion criteria, participants will receive detailed information about the study and will provide written informed consent prior to any study-specific procedures.

Assessments will be conducted in the patient’s room, either self-administered or assisted by a researcher following a standardized script to ensure consistency in data collection (Table 1).

On the day of admission (Day 1), a comprehensive baseline assessment will be performed, including questionnaires (SARC-F, EORTC QLQ-C30, and PSQI), HGS measurement, body composition assessment using bioelectrical impedance, electromyographic recording of selected muscles, and blood sampling for serum biomarker determination.

From Day 2 until the penultimate day of hospitalization, daily functional assessments will be performed, consisting of HGS measurement and an sEMG protocol for neuromuscular fatigue characterization. These assessments will be scheduled in coordination with the clinical team to avoid interference with medical or therapeutic procedures.

On the day of hospital discharge, the full assessment performed at admission will be repeated, allowing analysis of absolute admission-to-discharge changes in both primary and secondary outcomes.

All evaluations will follow previously described standardized procedures, including quality control measures, periodic equipment calibration, and systematic recording of clinical events that may influence measurements. The assessment schedule (Table 1) is designed to integrate into routine clinical practice, minimizing patient burden while always ensuring safety.

### 3.6. Criteria for Suspending/Omitting Measurements

Measurements will be suspended in the presence of fever > 38 °C, symptomatic hypotension, moderate-to-severe pain, nausea, or clinical events that compromise participation. The possibility of omitting measurements on specific days is considered part of the ethical and pragmatic management of research in hospitalized oncology patients.

